**Methods/Design:**

Sixty patients with stable angina will be recruited and randomised 1:1 to exercise training or conventional care. Patients randomised to exercise training will attend an exercise physiology laboratory up to three times weekly for supervised aerobic interval training sessions of one hour in total duration. Patients will undergo assessments of angina, anxiety, depression, and peripheral blood gene expression at baseline, after six and twelve weeks of training, and twelve weeks after formal exercise training ceases.

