### Sample size calculation

As our primary outcome measure is gene expression in whole blood, *a priori *sample size calculations are not possible. Based on the pilot study guidelines of [22], we will recruit 30 volunteers for each group, making a total sample size of 60. The results of this pilot will provide information on recruitment, compliance and attrition, and will identify logistical constraints that might limit the number of potential recruits. Variability data for the outcome measures and estimates of the treatment effect could be used to inform design a subsequent larger-scale randomised controlled trial, if post hoc analysis reveals this initial study to be underpowered.

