### Statistical analysis

Outcomes will be compared at each assessment point using a mixed-design factorial ANOVA. Where any significant difference existed at baseline between groups, ANCOVA procedures will be implemented, with baseline values used as the covariate [23]. Statistical significance will be set at *p *< 0.05. Bivariate relationships between exercise tolerance and other outcome variables will be evaluated using Pearson's correlation analysis. Data will be analysed using SPSS (SPSS U.K. Ltd, Woking U.K.). The data will be analysed on an intention to treat basis with all analyses including missing data by imputing change across time to be zero. Parametric data will be presented as mean differences of change scores between time points, with 95% confidence intervals and effect sizes (calculated as Cohen's *d *i.e. mean of the treatment effect divided by the standard deviation of the controls). Gene expression data will be analysed using our previously published probabilistic method for analysis of microarray data that improves probe level sensitivity [24-26].

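### Outcomes sent to ANCOVA for a baseline difference are still to be presented as change-score differences, so the reported estimate and interval need not match the p-value

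*Protocol article*

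**What the plan says.** All of this is in the Statistical analysis section of the protocol article, except the sample size.

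- Default test: "Outcomes will be compared at each assessment point using a mixed-design factorial ANOVA".
- Switch: "Where any significant difference existed at baseline between groups, ANCOVA procedures will be implemented, with baseline values used as the covariate".
- Significance level: 0.05. Sidedness is not stated.
- Presentation: "Parametric data will be presented as mean differences of change scores between time points, with 95% confidence intervals and effect sizes". The effect size is Cohen's d, the treatment effect divided by the control-group standard deviation.
- Missing values are handled by imputing zero change.
- Gene expression, named as the primary outcome under Sample size calculation, is analysed by a separate probabilistic method.
- Sample size: "we will recruit 30 volunteers for each group, making a total sample size of 60".

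The presentation rule applies to parametric data in general. It does not distinguish outcomes analysed by mixed ANOVA from those analysed by ANCOVA, and it does not say whether the differences are adjusted for baseline.

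**The concern.** In the default branch, test and estimate belong together: with two time points, the group-by-time term of a mixed ANOVA is a t-test on change scores. In the ANCOVA branch they separate. ANCOVA removes the baseline gap multiplied by a fitted slope b, whereas a raw change score removes the whole gap, as if b were 1. The two estimates differ by (1 − b) times the baseline gap. The plan enters ANCOVA because that gap is large, so the disagreement is greatest where ANCOVA is used. When b is below 1 the change score over-corrects, and the arm that started worse appears to gain more.

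The reported estimate matters here. The Sample size calculation section says that effect estimates and variability data from this pilot could inform a larger trial. A reader designing that trial would take the mean difference, interval and Cohen's d, not the p-value.

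**Working it through.** **Inputs from the article.** 30 per arm, 1:1 allocation, significance level 0.05, nominal 95% intervals. The sample size of 60 is 2 × 30 from a pilot-study guideline. The article gives no effect size, standard deviation or power, so there is no power calculation to reproduce. The figure to test is the nominal 95%.

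**Assumptions.** Two-sided tests, normal data, equal standard deviations (SD = 1), no dropout unless stated, ANCOVA triggered by a baseline difference in the same outcome, and a baseline-to-follow-up correlation ρ of 0.3, 0.5 or 0.7. With equal SDs the ANCOVA slope is about ρ.

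**1. Gap needed to trigger ANCOVA.** The standard error of the baseline difference is SE0 = √(2/30) = 0.258 SD. The trigger is t(0.975, 58 df) × SE0 = 2.00 × 0.258 = 0.52 SD. Under sound randomisation it fires for 5% of outcomes.

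**2. Mean gap once triggered.** For a standard normal z, the mean of |z| given |z| > 1.96 is 2 × 0.0584 / 0.05 = 2.34. The mean gap is therefore 2.34 × 0.258 = 0.60 SD.

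**3. Distance between the two estimates.** (1 − ρ) × 0.60 = 0.42, 0.30 and 0.18 SD for ρ = 0.3, 0.5 and 0.7.

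**4. Coverage of the change-score interval given the trigger, by hand.** The standard error of the change-score difference is √(2(1 − ρ)) × SE0. In those units:

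- bias at the mean gap = 2.34 × √((1 − ρ)/2)
- remaining spread, given the baseline gap = √((1 + ρ)/2)
- coverage ≈ Φ((1.96 − bias)/spread), the other tail being negligible

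| ρ | bias | spread | (1.96 − bias)/spread | coverage |
|---|---|---|---|---|
| 0.3 | 1.38 | 0.81 | 0.71 | 76% |
| 0.5 | 1.17 | 0.87 | 0.91 | 82% |
| 0.7 | 0.91 | 0.92 | 1.14 | 87% |

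**5. Simulation.** Simulated trials with 30 per arm, keeping those with a significant baseline difference, agree with the hand calculation to within about one percentage point:

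| ρ | change-score CI coverage | CI and ANCOVA p-value disagree, no effect | disagree, true effect 0.5 SD |
|---|---|---|---|
| 0.3 | about 76% | 24% | 43% |
| 0.5 | about 82% | 18% | 41% |
| 0.7 | about 87% | 12% | 30% |

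The ANCOVA interval covers about 95% in the same trials. Over ρ from 0.1 to 0.9, change-score coverage given the trigger runs from about 70% to 92%.

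**6. All trials.** Without selecting on the baseline test, the change-score interval covers 95%.

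**7. Zero-change imputation.** Setting follow-up equal to baseline pulls the slope towards 1. With 20% of values imputed at random and no treatment effect, coverage given the trigger rises to about 80% to 89% for ρ = 0.3 to 0.7.

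**8. Width if ANCOVA were used throughout.** The ratio of change-score to ANCOVA interval width is about √(2/(1 + ρ)) = 1.24, 1.15 and 1.08, so the change-score interval is 24%, 15% or 8% wider.

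**The case against.** The strongest reply is that the article never calls the presented differences unadjusted. ANCOVA fitted to change scores with baseline as covariate gives a baseline-adjusted mean difference of change, with the same treatment effect, interval and p-value as ANCOVA on follow-up values. That would also satisfy the presentation sentence, and the conflict would vanish. A condensed article may leave such detail to the full protocol. This stands in part: a reader might infer that the plan fixes unadjusted reporting after ANCOVA, and the text does not go that far. What remains is that the rule is written for all parametric outcomes, its ordinary meaning is raw change, and it therefore permits the mismatched interval.

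Further limits also stand:

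- A reader might infer that the trial's intervals under-cover in general. They do not. The shortfall is conditional on the trigger.
- A reader might also infer that change-score intervals would be wrong even if ANCOVA were used for every outcome. Over all trials they still have 95% coverage and are only less precise.
- The coverage figures depend on a correlation that the article does not give.
- The switch refers to any significant baseline difference. If imbalance in another variable can trigger ANCOVA, the 0.52 SD minimum gap does not apply to the outcome analysed, and the shortfall for a roughly balanced outcome is smaller.
- With four independent outcomes, at least one would trigger ANCOVA in 1 − 0.95⁴ = 18.5% of trials. Outcomes measured in the same patients are unlikely to be independent, so this is only a guide.
- The larger trial is a possibility, conditional on this one proving underpowered, not a commitment.

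**Conclusion.** The point holds as a reporting rule that does not follow the plan's own change of model. On the ordinary reading, for an outcome that triggers ANCOVA, the presented difference is shifted towards the arm that started worse by an average of about 0.2 to 0.4 SD, and its interval disagrees with the ANCOVA p-value about significance in a substantial minority of cases. These sizes rest on the assumptions listed in the working, above all a correlation of 0.3 to 0.7. They concern roughly one outcome in twenty and only outcomes other than gene expression. The documents do not support a claim that unadjusted reporting is certain, or that the trial's intervals are invalid overall. The rule is still worth correcting, because the affected estimates would be carried forward and the correction needs no new data.

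**What to change.** At minimum, add to the Statistical analysis section: *Wherever ANCOVA is used, the baseline-adjusted difference between arms, its 95% confidence interval and the standardised effect will be taken from that ANCOVA. Raw change scores by arm will be shown as description only.* Interval and p-value then agree by construction, and coverage given the trigger returns to about 95%.

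Preferably, use baseline-adjusted ANCOVA for every continuous clinical outcome, whatever a baseline test shows. The default mixed ANOVA contains no baseline covariate, so a rule requiring adjusted differences for all outcomes works only if the model is changed as well. This makes the presentation rule consistent throughout and gives narrower intervals than change scores.

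Cost: a small rewrite of the analysis paragraph and slightly more analysis work. No additional patients, visits or measurements are needed.
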